## Description of statistical methods

First, we will begin with descriptive analysis of all data by site, using means, variances, quartiles, and graphical assessments of the distribution and skewness of the data. We will describe feasibility and acceptability measures at the participant level.

Then, we will proceed with a pre-post intervention analysis using the Hopkins Symptoms Checklist as a main outcome to compare mental health symptoms before and after receiving the intervention. Moreover, on a second phase, we will calculate effect sizes and trends of effectiveness between intervention group and the non-treated group from the parent trial using endline data from parent trial.

We will use standard linear regression models to assess the impact of the intervention arm on mother’s mental health and mother-child relationship. The intervention outcome variable will be SRQ-20 used as a dichotomous variable with the cutoff at seven. Separate models will be estimated with and without baseline covariates.

The feasibility, acceptability, and difficulties and successes in carrying out research and intervention activities will be explored through a mix-methods analysis including dosage analysis (attendance to the intervention’s sessions) and semi-structured interviews with the participants and focus group with intervention’s providers. The burden of completing the assessments and PM+FM on the time and effort of participants, satisfaction with the intervention, and barriers and facilitators to adherence will be explored through semi-structured interviews with all the participants enrolled in the intervention arm (including participants that have dropped out). Qualitative data resulting from the open-ended questions to participants and focus groups with WCHWs will be transcribed, coded and analysed using a thematic approach to inform on feasibility, acceptability, and explain the potential efficacy of the PM+FM intervention

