| **Outcome (s)** | The primary study outcomes will be 1) number of sessions of PM+ attended (acceptance of the program = >50% of sessions attended; feasability within the local context = ≥ 1 session attended and offered and participants’ and providers’ qualitative feedback) and 2) improve their mental health status (overall mental health symptoms by SRQ-20 <7; Hopkins Symtpoms checklist reduction (% of cutoff <1.0.6),  Secondary outcomes: Patient Health Questionnaire (PHQ-9) (0-27; cutoff score, >10) for depressive symptoms; Generalized Anxiety Disorder Scale (GAD-7) score range, 0-21; cutoff score, >10) for generalized anxiety symptoms; Psychlops, psychological outcome profiles (designed to evaluate problem management plus intervention) and World bank toolkit on child-mother relationship. |
| **Study Design** | Randomised control trial |
| **Inclusion/Exclusion Criteria** | All mothers enrolled in Zamcharts clinical trial (n=790) with SRQ-20>7.  Exclusion criteria:   - Mothers who plan to migrate out of the study area within 6 months of the enrolment date - Mothers with severe substance use symptoms, bipolar disorder or squizophrenia - Mothers receiving psychotherapy elsewhere |
| **Measurements and Procedures** | From the total of 265 mothers residing in Lusaka district participating in the ZamCharts study and with mental health needs, we will divide them into two groups:  a control group a intervention group  All women will be called for a screening interview and then, if eligible, invited to receive a baseline interview followed by the intervention (provided in health facilities, by phone and at home) at the beginning and an endline interview at the end of the study.  Families in the intervention group will receive a locally adapted version of the Problem-Management Puls intervention developed by WHO after the baseline interview that allows them to better manage life stressors. The intervention will be provided by trained community health workers, started in groups (1^st^ session) and then continued individually by phone, or in-person at health facilities or at women’s home.  Severe cases will be referred to psychiatry services to evaluate need of antidepressants. |
| **Study Product/Intervention according to KlinV, if applicable** | This study will test an intervention: Problem Management+For Moms (PM+FM) program to reduce mental health symptoms among women and increase mother-child interaction |

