| **Comparator(s) (if applicable)** | The comparator for the interventions is standard local caregiving (no intervention) among mothers participating in the Zamcharts clinical trial |
| **Study Duration** | 9 Months |
| **Participants** | A total of 265 caregivers and their children are expected to participate in the study. |
| **Study Schedule** | Sept. 2022: study setup, software development and IRB approval. Identification of WCW  Sept. 2022 – Nov. 2022: Training of 3-5 WCW  Nov. 2022: Enrollment of participants. Screening.  Dec. 2022 – April 2023: implementation of interventions  April 2023: Endline assessments  May 2023 - December 2023: Data analysis & dissemination |
| **Study Centre(s)** | The study will be coordinated by the PIs, and implemented by Innovations for Poverty Action Zambia in direct collaboration with the Zambian Ministry of Health and the department of psychiatry of the University Teaching Hospital in Lusaka. |
| **Statistical Considerations & Power calculations** | The study is statistically powered to detect a 0.25 SD improvement in SRQ-20 over an 6-month period between mothers receiving the PM+FM and mothers not receiving the intervention, assuming α=0.05, a follow-up rate of 85% (attrition < 15%), and an intra-class correlation coefficient (ICC) of 0.05 . The estimated improvement is based on the results from similar studies. |
| **Ethical Statement** | This study will be conducted in compliance with the protocol, the current version of the Declaration of Helsinki, KFPE principles for transboundary research as well as all national legal and regulatory requirements. |

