Each enrolled participant will be assigned a specifically trained CHW, that we will call Wellbeing-Community Worker (WCW). WCWs will conduct a welcome call to their assigned participant and provide 10-12 individual sessions of the PM+FM intervention.

In a first step, we will assess efficacy by re-evaluating mental health symptoms (using HSCL-25) of caregivers again 5 months after the intervention. In a second step, we will compare changes in mental health at the population level using data from the larger study. Specifically, we will use endline data to be collected in the second quarter of 2023 to look at mid-term mental health outcomes (SRQ-20) as well as caregiver-child interactions and child developmental outcomes.

Qualitative data will be collected through semi-structured interview to participants during treatment completion assessment (5 months after enrollment) and focus groups with WCWs providing the intervention (analyzed using thematic approach to inform and complement quantitative results on feasibility, acceptability, and efficacy of the PM+FM intervention.

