- **Training and Supervision of WHW:** We will identify 4 to 6 people with at least a high school diploma, with some previous experience of working within the community and interested in mental health topics to be trained as WCWs. The training program occur in 4 full days of instruction followed by 4 weeks of role-plays with 2 hours weekly group supervision. Instructional training starts by addressing program objectives, ethics, emergency protocol procedures, psychoeducation about common mental health problems (day 1) and basic components of psychotherapy (i.e. motivational interviewing, cultural formulation, mindfulness practice and problem solving technique (Day 2). During the third and fourth day of instructional training, we will focus on the specific sessions’ content, special clinical situations (i.e. substance use involvement, domestic violence, and suicidal thoughts), and training related to their integration in the clinical site, including communication and referral procedures. It will end with a review of the emergency protocol procedures. Instructional trainings will be videotaped for further use for needed subsequent trainings. After roleplaying with two example cases and receiving weekly supervision. WCWs will deliver the intervention to two first cases as pilots. Pilot cases (ineligible for the trial because of mild symptoms or because already receiving treatment). All role-plays and pilot sessions will be audiotaped, transcribed and heard by the supervisor. The **supervision protocol** includes weekly individual and group supervision throughout the training process (individual supervision) and trial (group supervision) to support the WCWs and provide feedback on the session tapes, share the fidelity forms and to resolve issues related to the delivery (e.g. severe cases and drifting). We plan to collect data on training needs and mental health basic knowledge among the WCWs at the moment of hiring and every 6 months to evaluate mental health care delivery capacity. The supervisor will be a local psychologist specially trained by the PI of this project.

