## 7.2. Sample size calculation

This is a pilot study nested within the “The impact of growthcharts on stunting and caregiver awareness: research and policy engagement for potential scaling (ref. no. 1411-2020)” clinical trial. 800 caregiver-child dyads were enrolled in this study in Lusaka in 2021; 28% of these women displayed mild to severe symptoms of depression and/or anxiety (SRQ-20 ≥ 8). For this feasibility study, 30% of the women enrolled in the parent trial displayed mild to severe symptoms of depression and/or anxiety (SRQ-20 ≥8). For this study, we expect an attrition rate of 13% based on previous studies. With an expected analytical sample size of 100 women per arm we are powered to detect an intent-to-treat difference of 20 percentage points in the prevalence of depression at endline with power 0.8, and 23 percentage point difference in depression with power 0.9. We are aware that for the current trial we are not powered to detect small effect size. Thus, we will only explore the efficacy of the intervention to generate some preliminary efficacy estimates that will serve us to power and elucidate the needed sample size for a larger effectiveness trial.

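### The synopsis assumes an ICC of 0.05 for an unnamed cluster, but neither the standard regression nor the section 7.2 power allows for any clustering, including that by community worker in the treated arm

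*Protocol*

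**What the plan says.** **Power statements.** The synopsis (Statistical Considerations & Power calculations) describes the study as "powered to detect a 0.25 SD improvement in SRQ-20 over an 6-month period" and lists "an intra-class correlation coefficient (ICC) of 0.05" among its assumptions. It does not say what the clusters are, and it gives no power value. Section 7.2 makes a different calculation: "With an expected analytical sample size of 100 women per arm", it claims power 0.8 for a 20-point difference in depression prevalence and 0.9 for 23 points. It mentions neither an ICC nor a design effect, and it does not state the control rate.

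**Delivery.** Women are randomised individually, 1:1. Under Study design, "Each enrolled participant will be assigned a specifically trained CHW". The number of workers varies: three to five in the synopsis schedule, four to six in the Schedule of events, and in the training paragraph "We will identify 4 to 6 people with at least a high school diploma". The comparator section gives controls no intervention. The synopsis also describes delivery as "started in groups (1^st^ session) and then continued individually by phone", whereas Study design and the intervention section describe individual sessions.

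**Analysis.** Description of statistical methods says "We will use standard linear regression models to assess the impact of the intervention arm", with SRQ-20 dichotomised and models fitted with and without baseline covariates. No section mentions a worker effect, a mixed model or cluster-robust standard errors.

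**The concern.** The protocol assumes correlated outcomes in one place, then names a model and gives a power figure that treat all women as independent. The obvious source of correlation is the worker. Each treated woman shares a WCW with many others, and no control does, so any such clustering sits in one arm only. Ordinary regression counts the treated women as independent, which makes the standard error of the arm effect too small whenever workers differ in their results.

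At stake are intervals that are too narrow, p-values that are too small and an optimistic power statement. Section 7.2 also says the estimates will be used to size a larger trial. That use needs honest uncertainty and a WCW-level ICC, which the plan does not set out to estimate.

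**Working it through.** **Inputs from the protocol.** 100 analysed per arm, 20 points at power 0.8 and 23 points at 0.9 (section 7.2); ICC 0.05, alpha 0.05 and 85% follow-up (synopsis); three to six workers (range across the synopsis, Schedule of events and training paragraph).

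**Assumptions of this check.** Two-sided test; ICC at WCW level; equal caseloads; control rate 60%, because none is given.

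**1. The plan's own figure.** A two-proportion test with pooled variance, no continuity correction and no design effect gives, at 100 per arm:
- 60% v 40%: power 0.812 (97 per arm needed for 0.8).
- 60% v 37%: power 0.908 (98 per arm needed for 0.9).

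Both match section 7.2 with no clustering. At a 60% control rate there is no room for a design effect. A much higher control rate, near 90%, would leave some room (62 and 65 per arm needed), but section 7.2 states neither such a rate nor a design effect.

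**2. One-arm clustering at ICC 0.05.** With m = 100 / workers:
- treated-arm design effect DE = 1 + (m − 1) × 0.05; control-arm design effect = 1
- variance ratio VR = (DE + 1) / 2
- true SE / reported SE = √VR; shortfall = 1 − 1/√VR
- true error of a nominal 5% test = 2Φ(−1.96/√VR)

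Example, five workers: m = 20; DE = 1 + 19 × 0.05 = 1.95; VR = 1.475; √VR = 1.214; error = 2Φ(−1.614) = 10.7%.

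| Workers | m | DE | VR | SE ratio | SE shortfall | True error | Power 60 v 40 | Power 60 v 37 |
|---|---|---|---|---|---|---|---|---|
| 6 | 16.7 | 1.78 | 1.39 | 1.180 | 15% | 9.7% | 67% | 79% |
| 5 | 20.0 | 1.95 | 1.475 | 1.214 | 18% | 10.7% | 65% | 77% |
| 4 | 25.0 | 2.20 | 1.60 | 1.265 | 21% | 12.1% | 61% | 74% |
| 3 | 33.3 | 2.62 | 1.81 | 1.345 | 26% | 14.5% | 56% | 68% |

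The power columns inflate both variances by VR and use a normal approximation. With so few workers, small-sample degrees of freedom would lower them further.

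Simulated ordinary regression agrees: 9.8–14.6% for a continuous outcome and 10.5–15.4% for a binary outcome with a 50% event rate. If the 0.05 is on a latent scale behind the dichotomised score, the binary result is lower, 8.3–12.1%.

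**3. Sensitivity of the true error (six to three workers).**
- 100 per arm, ICC 0.02: 6.8–8.8%.
- 100 per arm, ICC 0.01: 5.9–6.9%.
- 35 per arm (the roughly 70 women in Study design and Exclusion criteria), ICC 0.05: 6.4–8.2%.
- 113 per arm (265 × 0.85 / 2, from the synopsis), ICC 0.05: 10.3–15.7%.
- ICC 0.05 for enumeration areas, women randomised individually: about 5% by simulation, because each area contributes to both arms.

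**The case against.** The strongest objection is that the protocol never says the 0.05 belongs to workers. The Recruitment section describes enumeration areas, which are an equally natural source. Under individual randomisation an area-level ICC leaves the error near 5%. This stands. A reader might infer that the plan doubles its type I error, but the documents do not support that as a plain statement. It requires a WCW-level ICC of about 0.05 and about 100 women per arm. With the roughly 70 women expected elsewhere in the protocol, the inflation is modest. The 14.5% figure also needs three workers, the low end of the synopsis range only.

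Second, the inflation depends on what is being inferred. If the target is the effect delivered by these particular workers, their differences are part of the treatment. If the intervention does nothing for anyone, delivery by workers should create little clustering. This limits the type I error argument. It does not rescue the intervals when workers do differ and the result is meant to inform a wider programme, which is the protocol's stated long-term aim.

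Third, section 7.2 calls efficacy exploratory, and standard-error methods can be left to a SAP. The first point lowers the consequence. The second does not remove the conflict, since the protocol itself states an ICC and then a model and a power figure without it.

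Fourth, three to six workers estimate a variance component poorly. That is true, and it calls for a sensitivity range; it does not justify assuming zero.

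**Conclusion.** The concern holds in conditional form. It is certain that the ICC of 0.05 has no named cluster, that section 7.2 states no allowance for it, and that the named regression ignores worker clustering present in one arm by design.

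The size depends on an assumption. If 0.05 is the WCW-level ICC and 100 women per arm are analysed, the reported standard error falls 15–26% short of the true one and the nominal 5% test runs at about 10–15%. Power for 60% v 40% is then about 56–67% instead of 81%, and for 60% v 37% about 68–79% instead of 91%. With a smaller ICC, about 70 women in all, or an area-level ICC, the error lies between about 5% and 9%. The change should be made, but the trial's feasibility and acceptability aims do not depend on it.

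**What to change.** - State which cluster the 0.05 refers to, and reconcile the synopsis power statement with section 7.2. If it is the WCW, restate section 7.2 power with the one-arm design effect and give the assumed control rate and number of workers.
- Record the WCW identifier for every treated woman. Reconcile the group and individual descriptions of the first session, and record the group identifier if groups are used.
- Replace or accompany the standard regression with a partially nested model: a random WCW effect in the intervention arm only, with small-sample degrees of freedom.
- Report the WCW ICC with its uncertainty, and repeat the analysis over a range of fixed ICC values, since three to six workers cannot estimate it well.
- Do not simply delete the ICC. That would remove the visible conflict and leave worker clustering untreated.

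The cost is analysis wording, one or two identifier variables and a restated power figure. The downside is wider intervals and, if the ICC is at WCW level, a lower stated power.

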### Datasets to be analysed, analysis populations

The final analysis will primarily rely on the data collected in the endline survey. Baseline variables will be used to 1) assess the extent to which balance was reached through the randomization and 2) create a set of control variables used in adjusted models.

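### The between-arm analysis cuts SRQ-20 at seven, giving up roughly a third to a half of its information, and does not test the 0.25 SD shift for which the synopsis claims power

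*Protocol*

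**What the plan says.** Protocol, Description of statistical methods: "We will use standard linear regression models to assess the impact of the intervention arm" on maternal mental health and the mother-child relationship. Then: "The intervention outcome variable will be SRQ-20 used as a dichotomous variable with the cutoff at seven". And: "Separate models will be estimated with and without baseline covariates". Under Datasets to be analysed, baseline variables serve to check balance and to "create a set of control variables used in adjusted models"; baseline SRQ-20 is not named among them.

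Three other places use the binary form. The synopsis outcome row gives SRQ-20 below 7. The Primary endpoint section gives SRQ-20 of 7 or less at 6 months, and/or an HSCL-25 criterion. Section 7.2 gives power for a 20-point difference in endline depression prevalence (power 0.8) and a 23-point difference (power 0.9), with 100 women analysed per arm.

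One place does not. The synopsis row on statistical considerations says: "The study is statistically powered to detect a 0.25 SD improvement in SRQ-20 over an 6-month period", with alpha 0.05, 85% follow-up and "an intra-class correlation coefficient (ICC) of 0.05".

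The full score is available. Eligibility rests on a fresh SRQ-20 assessment (Study design), and Table 1 of measures lists SRQ-20 at enrolment and 6 months.

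**The concern.** A shift in SD units is a statement about the mean score. A model of scores above or below seven estimates a difference in proportions. The synopsis therefore claims power for a quantity that the stated between-arm analysis does not produce.

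The cut also costs precision. Every woman enters with a score above 7. A fall from 8 to 7 counts as full success, while a fall from 19 to 9 counts as no change. Section 7.2 concedes that small effects are out of reach and gives the purpose as preliminary efficacy estimates for planning a larger trial. A mean difference with its SD would serve that purpose directly, and the planned between-arm model yields neither.

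**Working it through.** **Inputs.** 100 analysed per arm and effects of 20 and 23 points (section 7.2); 0.25 SD and alpha 0.05 (synopsis); 265 participants and 85% follow-up (synopsis); 1:1 allocation (Study design). Assumed because not stated: two-sided test, control prevalence, shape of the score, baseline-endline correlation r. No design effect is applied, because no cluster size accompanies the ICC.

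**1. The plan's own binary figure.** n per arm = [1.96·√(2·p̄(1−p̄)) + z_power·√(p1(1−p1) + p2(1−p2))]² / (p1−p2)².

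- 60% vs 40%, power 0.8: (1.96·0.707 + 0.842·0.693)² / 0.04 = 97.
- 60% vs 37%, power 0.9: (1.96·0.707 + 1.282·0.688)² / 0.0529 = 98.

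Section 7.2 reproduces at a control prevalence near 60%.

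**2. The synopsis figure.** n per arm for 0.25 SD at 80% power = 2·(1.960 + 0.842)² / 0.25² = 252. Power at 100 per arm on the score = Φ(0.25·√(100/2) − 1.96) = Φ(−0.19) = 42%. The synopsis's own 265 × 0.85 / 2 = 112.6 per arm gives 47%.

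On the dichotomy, with 60% of controls above the cut, a 0.25 SD shift of a normal score moves 60% to 50.1%, and power at 100 per arm is 29%. For control prevalences of 30% to 70% it is 25-29%.

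**3. Information lost by the cut (normal score).** Share retained = φ(z_p)² / [p(1−p)], where p is the share above the cut.

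| p | Retained | Lost |
|---|---|---|
| 0.5 | 0.637 | 36% |
| 0.6 or 0.4 | 0.622 | 38% |
| 0.7 or 0.3 | 0.576 | 42% |
| 0.8 or 0.2 | 0.490 | 51% |

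So 100 women per arm carry the information of 49-64.

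**4. Sensitivity to shape.** For a beta-binomial 0-20 score cut above 7 (means 5-10, SDs about 3.3-6.6), retained information is 0.52-0.69, a loss of about 31-48%. It falls below one third only with wide dispersion (SD about 5.7 or more).

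**5. What the full score buys.** 60% vs 40% equals a normal shift of 0.253 + 0.253 = 0.507 SD. On the score this needs 2·2.802² / 0.507² = 62 per arm, against 97 on the dichotomy. With baseline adjustment at an assumed r of 0.5, multiply by 1 − r² = 0.75: 46 per arm. At 100 per arm, power for this effect rises from 81% to 95%.

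The detectable difference at 80% power and 100 per arm is 2.802·√(2(1−r²)/100): 0.396 SD at r = 0, 0.378 at 0.3 and 0.343 at 0.5.

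**6. If recruitment is nearer the other stated figure.** Study design expects about 70 eligible women. With the 13% attrition of section 7.2, 70 × 0.87 / 2 is about 30 per arm. The unadjusted score then detects 0.72 SD at 80% power, and power for 0.25 SD is 16%.

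**The case against.** The best defence is that the dichotomy is a coherent choice. It mirrors the entry criterion, reads clinically as remission, and matches the synopsis outcome row, the primary endpoint and section 7.2. That stands. A reader might infer that powered and analysed endpoints conflict throughout the protocol; they do not. The outlier is the single 0.25 SD line in the synopsis. Agreement among the other sections does not remove the loss of precision.

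A reader might also infer that linear regression is wrong for a 0/1 outcome. It is not: regressing the indicator on arm estimates the risk difference, the quantity that section 7.2 powers. With equal arms the pooled residual variance is the average of the two arm variances, so unadjusted ordinary and robust standard errors nearly coincide.

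Nor does planning models with and without covariates show that both have equal standing. In a linear model under randomisation both target the same effect, and the lead model and covariate list may properly sit in an analysis plan that is not shown.

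Finally, the full score would not rescue the synopsis claim. Even with baseline adjustment, power for 0.25 SD at 100 per arm is 46%, 53% or 60% at an assumed r of 0.3, 0.5 or 0.6, and entry above 7 truncates the baseline and may hold r down.

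**Conclusion.** The point holds in two parts.

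- The synopsis claims power for a continuous-scale effect that the stated between-arm analysis does not test and that 100 women per arm would not detect adequately. The ICC of 0.05 could only lower these powers. This part rests on the protocol's own figures plus a two-sided test; the dichotomy's power also assumes a normal score.
- The cut discards a substantial share of the information in a score already measured at both time points. The size is conditional on the unstated score distribution, so a loss of more than one third is likely but not established.

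This is an inefficient choice and an unsupported power statement, not an invalid analysis. Because the trial is exploratory and meant to inform the next sample size, the change is worth making before the analysis.

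**What to change.** - In Description of statistical methods, make the lead between-arm effectiveness estimate the endline SRQ-20 total score regressed on arm and enrolment SRQ-20, among randomised women. Report the mean difference with its confidence interval, and the SD.
- Take the baseline from the reassessment that determines eligibility. Confirm that it is held for both arms, since one sentence in Study design mentions reassessment only for the intervention group.
- Keep SRQ-20 of 7 or less as a supporting risk difference, and the unadjusted model as sensitivity.
- Align the synopsis outcome row, the Primary endpoint section and section 7.2. In doing so, settle whether the cut is below 7 (synopsis) or 7 or less (Primary endpoint).
- Remove the 0.25 SD power claim from the synopsis, or restate it as the difference detectable at the expected number analysed, with any clustering assumption given in full.

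This needs no new data, visits or participants. It does reach beyond analysis wording, because endpoint and sample size text must change too. The mean difference also needs the remission rate beside it for clinical reading.
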